### Provisions for post-trial care {30}

Participants will be contacted to determine the progression and resolution of any new-onset symptoms that appear following the baseline visit. The study team will send reports of any grade 3 or higher adverse events to the participant’s medical provider(s) following their participation in the trial.

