• Adults 21–70 years of age • Active Crohn’s disease not in remission based on a CDAI score >150 • Willing to take isolated XN as a dietary supplement for 8 weeks • Willing to have blood drawn biweekly and fast for 10–12 h before blood draws • Willing and able to collect biweekly stool samples at home • Willing and able to collect a 24-h urine sample before each study visit • Able to speak, read, and understand English • Able to provide written informed consent • Non-smokers (including tobacco and Cannabis products in any delivery including cannabidiol) • For individuals of child-bearing potential, willing to use an intrauterine device or two other concurrent forms of birth control to prevent pregnancy while enrolled	• Variable dosing of anti-inflammatory medications >1×/week • Currently or recent (within last 14 days): o Taking any dietary supplements containing xanthohumol, flavonoids, or other “anti-inflammatories” including curcumin, turmeric, fenugreek, hops, rosemary, ginger, white willow, devil’s claw, fish oil (doses >1 g/day), or quercetin o Receiving intravenous nutrition support therapy o Taking anti-coagulant or anti-platelet prescription medications o Taking antibiotic, antiparasitic, or antifungal medications orally or intravenously o Initiated of or changes to supplements or medications o Initiated or changes to an exercise regimen o Initiated changes to a food plan o Involvement of a significant diet, weight loss, or very low-calorie liquid diet programs o Use of illicit drugs/substances o Participation in an interventional research study • Consumption of more than 1 beer per day or typical intake of more than 2 alcohol-containing beverages per day, more than 14 per week, or more than 4 in any single day within the past 14 days • Hospitalization (for any reason other than a scheduled medical procedure) within the last 3 months • Gastrointestinal surgery within the last 3 months • Malignancy within the last 5 years (except basal cell carcinoma, squamous cell carcinoma, and/or carcinoma in situ of the cervix) • Women who are lactating, pregnant, or planning pregnancy within the next 4 months • Do not have an active primary care provider or specialist (i.e., gastroenterologist) managing their CD

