The primary endpoint for laboratory values and vital sign measurements will be mean change from baseline to week 8, with changes also compared between groups from baseline to each additional follow-up visit (i.e., 2, 4, and 6 weeks). The frequency of new-onset or worsening laboratory values will be reported within groups throughout the trial at each biweekly visit. AEs and event severity will be reported as new-onset or worsening events spontaneously and at each biweekly visit. Together, these outcomes will provide a profile of safety and tolerability of 24mg XN for 8 weeks compared to placebo.

Secondary and exploratory outcomes include clinical disease activity, systemic inflammation (e.g., IL-10), intestinal permeability (e.g., intestinal fatty acid binding protein) and endotoxemia (e.g., LPS), platelet function, stool microbiome and bile acid composition, and the metabolic profile of XN in humans over 8 weeks. Each measurement will be collected at every biweekly clinical visit and compared between groups as mean change from baseline within groups and compared between groups at each follow-up visit. The primary endpoint for each secondary and exploratory outcome will be considered exploratory and reported as mean change within groups at week 8 from to baseline and compared between groups at each follow-up visit. The measurements to support these outcomes are outlined in Table 1.

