### Participant timeline {13}

The flow of participant involvement and descriptions of study visit procedures are described in Fig. 1. Participants will be screened by phone to determine initial eligibility. Within 30 days of initial eligibility confirmation, participants will complete an in-person clinical screening visit to further confirm eligibility. If the candidate remains eligible, they will be invited to complete baseline and randomization visits within 30 days of screening. All additional visits will occur biweekly for 8 weeks and follow the procedure flow according to Fig. 1 and Table 3.

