### Adverse event reporting and harms {22}

Adverse events will be assessed and graded according to severity at each biweekly clinical visit beginning at the baseline visit, as well as accepted via spontaneous report. Self-reported adverse events will be administered by verbal query through a standardized multi-system questionnaire based on the National Cancer Institute’s Common Technology Criteria for Adverse Events v4.0. Adverse events reported between study visits will be termed “spontaneous adverse events” and graded in a similar manner according to self-reported adverse events according to severity and duration. If an adverse event is of moderate or greater severity, the study team will coordinate with the patient’s physician and develop and document a response or monitoring plan.

Adverse events, both self-reported and spontaneous, will be detailed according to severity and length of duration and compared between groups. The presence of symptoms at baseline will inform the attributability of any symptom to the intervention. Worsening or new-onset symptoms after baseline will be considered potentially attributable to the intervention and will be determined according to prevalence in each group and a case-by-case basis by the study team and DSMB.

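### The post-trial resolution contact covers only new-onset symptoms, so a mild worsening of a baseline symptom still open at exit has no stated follow-up

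*Protocol article*

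**What the plan says.** Under Provisions for post-trial care {30} the article fixes the scope of the post-trial contact: "Participants will be contacted to determine the progression and resolution of any new-onset symptoms that appear following the baseline visit". In addition, that section provides for a report to the participant's medical provider for adverse events of grade 3 or higher.

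Three other sections define harm more widely:

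- Outcomes {12}: "AEs and event severity will be reported as new-onset or worsening events spontaneously and at each biweekly visit".
- Adverse event reporting and harms {22}: "Worsening or new-onset symptoms after baseline will be considered potentially attributable to the intervention". The same section says that adverse events "will be detailed according to severity and length of duration and compared between groups".
- Criteria for discontinuing or modifying allocated interventions {11b}: the halting rule counts events of at least moderate severity that are either new since baseline or getting progressively worse.

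For events of moderate or greater severity, section {22} has the study team coordinate with the participant's physician and "develop and document a response or monitoring plan".

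On the population, Eligibility criteria {10} require active disease, "not in remission based on a CDAI score >150". They exclude people who "Do not have an active primary care provider or specialist (i.e., gastroenterologist) managing their CD". On timing, Participant timeline {13} states: "All additional visits will occur biweekly for 8 weeks".

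**The concern.** The contact after the trial is narrower than the protocol's own definition of an adverse event. In a healthy population the difference would hardly matter, because most harm would be new. Here every participant starts with active Crohn's disease, so harm from the product may well show as more of a symptom that was already there. If such a symptom has worsened and is still open when visits end, the article states no step by which the study team learns whether it settled after the product was stopped.

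Two things are at stake, both modest. One is follow-up of the individual participant. The other is the completeness of the duration data that section {22} intends to compare between groups, and of the information available for its case-by-case attribution. Safety and tolerability are the main objective, so the follow-up rule should match the event definition.

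**Working it through.** There is no figure in the plan to reproduce. The check compares scopes and then bounds the number of participants affected.

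**Step 1: can new-onset be read to include worsening?** Sections {11b}, {12} and {22} each name the two as separate categories. Section {30} names only the first and ties it to symptoms that appear after the baseline visit. A symptom present at baseline does not appear afterwards. The natural reading is that worsened baseline symptoms fall outside the contact.

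**Step 2: what is stated for a symptom still open at exit?**

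| Severity | New-onset symptom | Worsened baseline symptom |
|---|---|---|
| Mild | Resolution contact {30} | Nothing stated for the study team |
| Moderate | Resolution contact {30} and plan {22} | Plan {22}; not stated to end or to continue at exit |
| Grade 3 or higher | Resolution contact {30}, plan {22}, provider report {30} | Plan {22} and provider report {30} |

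The only row in which a worsened symptom has no study-team provision at all is the mild one. In the other two rows the plan may already carry follow-up past exit, but no resolution contact is stated. The provider report sends information out; it is not stated to bring the outcome back.

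**Step 3: how many participants could the change reach?** Inputs: up to 32 randomized (Sample size {14}) and 15 completed on April 28, 2022 (Trial status).

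- Further participants still to exit: at most 32 − 15 = 17.
- If earlier completers were also contacted, the upper limit returns to 32.

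The article gives no rate of worsening events open at exit. The shares below are assumptions.

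| Assumed share | Of 17 still to exit | Of all 32 |
|---|---|---|
| 10% | 0.10 × 17 = 1.7 | 0.10 × 32 = 3.2 |
| 25% | 0.25 × 17 = 4.25 | 0.25 × 32 = 8 |
| 50% | 0.50 × 17 = 8.5 | 0.50 × 32 = 16 |

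The added contacts would be fewer where a participant is already being contacted about a new-onset symptom.

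**The case against.** The strongest case against is that this is an article, not the full protocol. Section {30} is two sentences; the Trial status section cites protocol version v1.13, which is not shown, and the figure and table that set out the visit procedures are not reproduced in the text at hand. Follow-up of open events is the sort of detail an article leaves out. That would be decisive if section {30} were silent. It is not: it states a scope, and the scope is narrower than the event definition used three times elsewhere. The unseen material could supply a wider rule, which is a reason for modest confidence but does not make the stated rule right.

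A second objection is that the sections do not contradict each other: recording and attributing events is one task, post-trial care another, and the second may be narrower. This stands in part. A reader might infer that worsening events are lost from the safety results. The article does not support that: they are recorded, graded, compared between groups and counted by the halting rule during the 8 weeks.

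A third objection is that clinically important worsening is already provided for. This also largely stands. A reader might infer that no worsened symptom of any severity is followed after exit. That goes too far, because the plan for moderate or greater events is not stated to stop at exit, and every participant must have a provider managing the disease. What remains uncovered is mild worsening, plus the lack of an explicit resolution contact above that level.

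Finally, section {22} names no criterion based on recovery after stopping the product, and Crohn's symptoms fluctuate, so the extra information for attribution is limited. That is fair, and it keeps the point small.

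**Conclusion.** The point holds as a cheap improvement. The stated post-trial contact omits a category of harm that the protocol itself counts, in a population where that category is foreseeable. The clear gap is a mild worsening of a pre-existing symptom that is unresolved at exit.

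The gain is slight: somewhat better follow-up of participants and somewhat more complete duration data. The rule is the same in both arms, and no primary analysis, power figure or halting threshold changes. The conclusion rests on two assumptions: that new-onset keeps in section {30} the meaning it has elsewhere, and that the full protocol does not already contain a wider rule.

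**What to change.** In Provisions for post-trial care {30}, keep the existing contact for new-onset symptoms and add any baseline symptom that worsened on study and is unresolved at exit. State that, for a worsened symptom, return to its baseline severity counts as resolution; complete disappearance of a chronic Crohn's symptom would be an unrealistic standard.

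The cost is one wording change and some extra contacts under a procedure that already exists, for at most 17 participants beyond the 15 completed on April 28, 2022. Applied only from the change onward, it would give earlier and later participants different follow-up. To avoid that, the sponsor can also contact earlier completers whose worsened symptoms were open at exit. Otherwise the date of the change should be reported alongside the duration data.

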### Outcomes {12}

The primary outcomes of the phase II trial include changes in laboratory toxicology measures, vital signs (blood pressure and heart rate), and AEs (Table 1). Assessment of laboratory measures to determine safety includes review for new-onset abnormalities (confirmed with repeat testing at the following clinical visit or as soon as possible following closeout, as applicable), including new-onset clinically significant elevation of liver function tests [aspartate transaminase (AST), alanine transaminase (ALT), bilirubin or alkaline phosphatase], new-onset anemia, elevations in creatinine, and/or reductions in estimated glomerular filtration rate (eGFR). Elevations of liver function tests will be considered “significant” if (1) abnormal per laboratory reference ranges and (2) represent a 25% deviation from previously observed values. New-onset anemia will be considered “significant” if (1) hemoglobin < 14 g/dL (140 g/L), hematocrit < 42% (< 0.42), or RBC < 4.5 million/mcL (< 4.5 × 10^12^/L) (for men); or hemoglobin < 12 g/dL (120 g/L), hematocrit < 37% (< 0.37), or RBC < 4 million/mcL (< 4 × 10 ^12^/L) (for women); *and* (2) values represent a 10% change or more from *baseline* values; *and* (3) values remain abnormal with repeat testing within 2 weeks. This threshold reduces reporting of new “borderline” abnormal values for participants with “high normal” baseline values. For elevations of creatinine, “significant” will be evaluated as greater than a 20% increase from *baseline* values, whereas reductions in eGFR will be considered as “significant” if greater than a 20% decrease from *baseline* values. A brief clinical interview will be conducted and recorded for all laboratory abnormalities not present at baseline to provide context, i.e., new-onset anemia tied to increased diarrheal episodes, etc. Serum calcium, potassium, and sodium; ɣ-glutamyl transferase (GGT); and blood urea nitrogen (BUN) to creatinine ratio (BUN:Cr) will also be collected to monitor electrolyte balance and provide additional measures of liver and kidney function, respectively.

The primary endpoint for laboratory values and vital sign measurements will be mean change from baseline to week 8, with changes also compared between groups from baseline to each additional follow-up visit (i.e., 2, 4, and 6 weeks). The frequency of new-onset or worsening laboratory values will be reported within groups throughout the trial at each biweekly visit. AEs and event severity will be reported as new-onset or worsening events spontaneously and at each biweekly visit. Together, these outcomes will provide a profile of safety and tolerability of 24mg XN for 8 weeks compared to placebo.

Secondary and exploratory outcomes include clinical disease activity, systemic inflammation (e.g., IL-10), intestinal permeability (e.g., intestinal fatty acid binding protein) and endotoxemia (e.g., LPS), platelet function, stool microbiome and bile acid composition, and the metabolic profile of XN in humans over 8 weeks. Each measurement will be collected at every biweekly clinical visit and compared between groups as mean change from baseline within groups and compared between groups at each follow-up visit. The primary endpoint for each secondary and exploratory outcome will be considered exploratory and reported as mean change within groups at week 8 from to baseline and compared between groups at each follow-up visit. The measurements to support these outcomes are outlined in Table 1.

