## Statistical methods

### Statistical method outcomes {20a}

Laboratory measures will be analyzed first with descriptive statistics including mean, median, and standard deviation. Distributions will be tested for skew and transformed (e.g., natural log) as needed to reduce skew on subsequent analyses. If distributions indicate substantial non-normality that cannot be modified with transformation, non-parametric tests (e.g., Wilcoxon rank-sum) will be used.

In addition, the frequency of new, clinically significant laboratory abnormal values as outlined above will be monitored by the DSMB. The percentage of these new abnormal values per reference ranges will be reported at each time point and compared between groups by Fisher’s exact test. Assessment for changes in the distribution of each parameter will be presented as means and confidence intervals (CI) within and between groups. The significance of differences will be compared using 2-sided, unpaired *t*-tests if normally distributed and a non-parametric Wilcoxon rank-sum test of mean values between groups if non-normally distributed. Overall increases and decreases in laboratory parameters will be tested using linear mixed ANOVA with time point as a repeated factor, potentially suggestive of cumulative toxicity if trending in a clinically deleterious direction. All factors will be considered significant if *p* < .05.

Clinical activity will be measured through the CDAI. A score >150 is considered *clinically active* and is an eligibility criterion. Changes in score from baseline between groups will be compared within groups using two-sided, unpaired *t*-tests at each interval with the primary outcome as a change in value from baseline to closeout, whereas within-group changes will be compared using two-sided, paired *t*-tests. Non-parametric Wilcoxon rank-sum test of mean values between groups will be used if data are non-normally distributed.

Measures within the PROMIS-29 v.2.0 questionnaire include seven validated subscales, i.e., physical function, anxiety, depression, pain intensity, pain interference, sleep disturbance, and social interaction. Analyses will be performed by calculating descriptive statistics of mean, median, and mode of reported *T*-scores and overall PROMIS-29 questionnaire and each subscale. Welch’s *t*-test will be used to test the differences in scores between groups with *p* < .05 considered significant.

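### For anemia and liver tests, the DSMB tally and the Fisher comparison cover only new abnormalities and omit worsening from an abnormal baseline, which the plan counts elsewhere

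*Protocol article*

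**What the plan says.** Outcomes {12} opens its laboratory criteria by saying that the assessment includes "review for new-onset abnormalities (confirmed with repeat testing at the following clinical visit", or soon after closeout, "including new-onset clinically significant elevation of liver function tests" and new-onset anemia.

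- **Liver tests.** An elevation is significant if it meets "1) abnormal per laboratory reference ranges and (2) represent a 25% deviation from previously observed values".
- **Anemia.** The rule begins "New-onset anemia will be considered “significant” if (1) hemoglobin < 14 g/dL (140 g/L), hematocrit < 42% (< 0.42" and gives parallel cut-offs for women (hemoglobin below 12 g/dL). It also requires a change of at least 10% from baseline and a repeat abnormal value within 2 weeks.
- **Creatinine and eGFR.** Each is judged on a change of more than 20% from baseline, with no condition on baseline status.
- **Clinical interview.** "A brief clinical interview will be conducted and recorded for all laboratory abnormalities not present at baseline to provide context".

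Later, the same section makes mean change from baseline to week 8 the primary laboratory endpoint and adds: "The frequency of new-onset or worsening laboratory values will be reported within groups throughout the trial at each biweekly visit".

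Statistical method outcomes {20a} says "the frequency of new, clinically significant laboratory abnormal values as outlined above will be monitored by the DSMB". The percentage of these new values is what Fisher's exact test compares between groups. That section also plans a mixed ANOVA on increases and decreases over time.

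Table 2 (Eligibility criteria {10}) requires active Crohn's disease and lists no laboratory exclusion.

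**The concern.** The plan uses two different event concepts for the same laboratory data. The count reported within groups covers new-onset or worsening values. The count that goes to the DSMB and is compared between groups covers new values only. For anemia and liver tests, the difference is the participant who enters outside the limit and then deteriorates.

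Such participants are eligible, and the plan foresees anemia from the disease itself: its example of context for a laboratory abnormality is anemia tied to increased diarrhea. If the new-onset label is followed, they sit in the denominator of the Fisher comparison for that analyte but cannot contribute an event. If an analyst applies only the numeric conditions, they can. Two competent analysts could therefore report different counts from the same data.

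This matters because the safety hypothesis (Hypotheses) and the first sample-size statement (Sample size {14}) are both framed as the frequency or proportion with laboratory abnormalities or adverse events, which is a categorical count.

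**Working it through.** **1. The plan's own figure.** Sample size {14} gives 12 per group and 25% attrition: 24 / (1 − 0.25) = 32, as stated. With an assumed 5% versus 55% event rate (the article gives no control rate), the usual two-proportion formula gives power 0.802 at 12 per group. Neither figure depends on how baseline-abnormal participants are classified.

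**2. The statements side by side.**

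| Where | What is counted or analyzed | Worsening from an abnormal baseline | Compared between groups |
|---|---|---|---|
| Outcomes {12}, liver and anemia criteria | new-onset | excluded by the label | not stated there |
| Outcomes {12}, creatinine and eGFR criteria | change from baseline | included | not stated there |
| Outcomes {12}, biweekly frequency | new-onset or worsening | included, no threshold for anemia or liver tests | no, within groups |
| {20a}, DSMB tally | new | excluded | – |
| {20a}, Fisher's exact test | new | excluded | yes |
| Outcomes {12}, mean change | all values | included | yes |
| {20a}, mixed ANOVA | all values | included | not stated |

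**3. Do the numeric conditions exclude these participants, or only the label?** The values below are illustrative. Fall = (baseline − follow-up) / baseline.

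- Woman, hemoglobin 13.2 to 11.8 g/dL: 1.4 / 13.2 = 10.6%, now below 12. If confirmed, she counts.
- Woman, 11.5 to 8.5 g/dL: 3.0 / 11.5 = 26.1%, below 12. She meets the cut-off and change conditions, and the third condition if the repeat is abnormal, but the anemia is not new.
- Man, 12.0 to 10.5 g/dL: 1.5 / 12.0 = 12.5%, below 14. Same position.
- ALT 60 to 90, upper limit assumed to be 40: 30 / 60 = 50%, above the limit. It meets both liver conditions, but the elevation is not new.

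So the numeric conditions do not require a normal baseline. Only the words new-onset and new remove the last three cases.

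**4. Can mean change stand in for the count?** A 3.0 g/dL fall in one of 12 participants moves the arm mean by 3.0 / 12 = 0.25 g/dL. The value is used in full, but one marked individual fall is hard to see in a mean.

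**5. Why a few participants matter.** Criteria for discontinuing {11b} halts the trial above 20% of participants: 0.20 × 32 = 6.4, so 7 participants; 0.20 × 24 = 4.8, so 5. At these numbers, whether two or three baseline-abnormal participants count could decide the result.

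**The case against.** The strongest reply is that worsening is not lost. The primary laboratory endpoint is mean change in all participants, also compared at weeks 2, 4 and 6. The mixed ANOVA looks for cumulative toxicity. Worsening values are reported at each visit. The laboratory assessment is said to include new-onset review, which is not exclusive wording. The DSMB also receives regular reports and considers worsening symptoms case by case. All of this stands, and it rules out two stronger readings.

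- **That a baseline-abnormal participant's deterioration never counts.** A reader might infer this from the new-onset labels, but it counts in three other places. The gap is confined to the DSMB tally and the Fisher test, for anemia and liver tests.
- **That a true difference in anemia would shrink to 50% to 75% of its size.** If a fraction f is anemic at baseline and cannot have an event, the observed difference is (1 − f) times the true one: 0.75 at f = 0.25 and 0.50 at f = 0.50. The documents give no f, and the formula also assumes an equal effect in anemic and non-anemic participants.

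The article condenses a fuller protocol, which may define worsening. The a priori critical laboratory values mentioned in {11b} are not listed here either. The absence of a threshold can therefore be stated only of the article. The inconsistency between Outcomes {12} and {20a} is on the page regardless.

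Whether the halting rule shares the gap is an inference. It refers to a listed criterion, and its qualifier about new or progressively worsening attaches most naturally to adverse events.

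**Conclusion.** The point holds in limited form. Read as written, worsening from an already abnormal baseline in anemia and liver tests is left out of the DSMB laboratory tally and the only categorical between-group laboratory test, while the plan counts it in a within-group report that has no threshold for those analytes. This is an inconsistency that should be resolved; it does not mean that the plan fails to observe deterioration.

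The conclusion rests on taking the labels at their word and on Table 2 admitting participants with abnormal baseline values. The size of the loss cannot be derived from the documents. No sample-size figure changes.

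**What to change.** In Outcomes {12} and {20a}, define the compared laboratory event as new-onset or worsening.

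- For a participant already outside the limit at baseline, apply the percentage the plan already uses for that analyte: 10% for anemia and 25% for liver tests, in the harmful direction and confirmed on repeat. The current text gives no direction for either percentage. It measures liver tests against previously observed values rather than baseline, so the reference value should be stated too.
- Use this one count for Fisher's test and the DSMB tables, and let the within-group report follow the same definition.
- Fix the wording before unblinding, so that the choice cannot depend on the results.

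The criterion referred to in the halting rule of {11b} must be reconciled with Outcomes {12} and {20a}. The sponsor should say explicitly whether a revised laboratory definition carries over to it; no halting rule is proposed here.

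The cost is a wording change, since the values are already collected at every biweekly visit. The small downside is a somewhat higher reported abnormality rate in both arms.

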### Criteria for discontinuing or modifying allocated interventions {11b}

Participants may elect to withdraw from the trial at any time for any reason. Participants may be withdrawn by the study team if they experience any new-onset, moderate or severe adverse events from the intervention. Any a priori-specified critical lab value observed and confirmed on repeat analysis and attributable to the intervention may also result in participant withdrawal. The trial will be halted if >20% of all participants demonstrate laboratory abnormalities in per the criterion listed *or* experience adverse events of moderate or greater severity which are new from baseline or progressively worsening.

No modifications of intervention dose or frequency of administration are allowed, and participants will be considered non-adherent and withdrawn from the trial if deviations from the dosing standard are reported to the study team. As XN was demonstrated as safe and tolerable in healthy adults at the same dosage and length of time in our phase I study [15], and is considered Generally Recognized as Safe [20], it is not anticipated that serious harms will require early discontinuation of the product or medical intervention to address the issue.

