### Sample size {14}

A sample size of at least 12 participants per group provides 80% power to detect ≥50% difference in the proportions of participants experiencing laboratory abnormalities or adverse events at a threshold of *α* = .05 by *χ*^2^ test. This sample size, at *n* = 12 per arm, provides >90% power using 2-sided *t*-tests to detect a mean change of 0.25–0.5pg/mL in TNF-α in the treatment arm according to preliminary data from previous pilot studies. Accounting for attrition up to 25%, we will randomize up to 32 participants. Attrition during the phase I trial was 10% [15].

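### No rule says how a laboratory abnormality counts when the participant leaves before the confirming repeat, so it may drop out of the between-group safety comparison

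*Protocol article*

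**What the plan says.** Outcomes {12} limits the safety review of laboratory tests to new-onset abnormalities that are "confirmed with repeat testing at the following clinical visit or as soon as possible following closeout, as applicable". It then gives numeric criteria for each test. For anemia a third condition is joined to the numeric ones: "values remain abnormal with repeat testing within 2 weeks". For liver tests, creatinine and eGFR, the need for a repeat comes only from the parenthesis quoted first.

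The plan expects people to leave early. Criteria for discontinuing or modifying allocated interventions {11b} states: "Participants may elect to withdraw from the trial at any time for any reason". It also lets the team withdraw participants for new moderate or severe adverse events, and withdraws those who report departures from the dosing standard. Sample size {14} adds: "Accounting for attrition up to 25%, we will randomize up to 32 participants". Attrition in the phase I trial is given there as 10%.

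Provisions for post-trial care {30} describes later contact about symptoms only: "Participants will be contacted to determine the progression and resolution of any new-onset symptoms that appear following the baseline visit". Statistical method outcomes {20a} compares the percentage of new abnormal values between groups at each time point by Fisher's exact test. The section on non-adherence and missing data {20c} makes every analysis per protocol, with multiple imputation of laboratory values as a sensitivity check.

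**The concern.** A confirmation rule is a reasonable guard against transient abnormalities, but it presumes that a second sample exists. For someone whose first abnormal value comes at the last visit before an early departure, the article neither says how the value is classified nor clearly provides for a repeat. Read literally, an anemia value with no repeat fails the definition. For the other tests the parenthesis leads to the same place.

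What matters is the direction of the error. If feeling unwell on XN makes both an abnormal value and an early exit more likely, the missing repeats fall mostly among harms on XN, and the comparison drifts towards a conclusion of safety. The proportion with laboratory abnormalities or adverse events is what Sample size {14} is built on and what Hypotheses uses to support safety. With so few participants, a single event can move the result.

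**Working it through.** **1. The plan's own figures.** Evaluable: 2 × 12 = 24. Randomized: 24 / (1 − 0.25) = 32, as stated. Up to 8 of 32 may therefore leave, about 4 per arm. At the phase I rate it would be 0.10 × 32 = 3.2, about 3 people.

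Sample size {14} says that a "sample size of at least 12 participants per group provides 80% power to detect ≥50% difference in the proportions of participants" with abnormalities or adverse events. No base rate is given. Assume 5% on placebo and 55% on XN, a two-sided 5% level and a pooled chi-square test without continuity correction. With p̄ = (0.05 + 0.55)/2 = 0.30:

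n = [1.960·√(2·0.30·0.70) + 0.842·√(0.05·0.95 + 0.55·0.45)]² / 0.50² = 11.9, so 12 per arm, with power 80.2%.

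At 10% against 60% the same formula gives 14 per arm and 76.2% power at 12, so the stated 80% needs a low placebo rate.

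**2. Which participants are affected.** Only those whose abnormality first appears at the last attended visit (week 2, 4 or 6). One seen earlier would already have had its repeat. Withdrawal for a critical laboratory value is outside this group, because {11b} requires that value to be confirmed first.

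**3. Effect if unrepeated values are not counted.** The power of Fisher's exact test is found by summing binomial probabilities over all tables with p < 0.05. All 16 per arm are kept, because 12 per arm is already net of attrition. Observed rate = true rate × (1 − share of events lost).

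| Events lost | XN / placebo observed (true 55% / 5%) | Power | XN / placebo observed (true 60% / 10%) | Power |
|---|---|---|---|---|
| none | 55% / 5% | 85.5% | 60% / 10% | 78.6% |
| 10%, XN only | 49.5% / 5% | 76.8% | 54% / 10% | 66.8% |
| 10%, both arms | 49.5% / 4.5% | 78.9% | 54% / 9% | 70.3% |
| 25%, XN only | 41.25% / 5% | 59.5% | 45% / 10% | 46.9% |
| 25%, both arms | 41.25% / 3.75% | 65.7% | 45% / 7.5% | 56.9% |

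**4. Effect if leavers are excluded instead.** Extreme case: 4 of 16 on XN leave, all with an unrepeated abnormality, and 4 leave placebo for unrelated reasons. Expected XN events are 0.55 × 16 = 8.8. The remaining rate is (8.8 − 4)/12 = 40%. Fisher power at 12 per arm is then 36%, against 69% if departures were unrelated to events.

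**5. One event.** 7/16 against 1/16 gives p = 0.037. With one XN event unconfirmed, 6/16 against 1/16 gives p = 0.083.

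**The case against.** The strongest reply is that much of the harm is captured elsewhere. Adverse events are themselves primary outcomes, are recorded at visits and spontaneously, and need no confirmation. Someone who leaves because of a new adverse event already counts in the combined proportion the trial is sized on. This stands: the selective loss is confined to people with an unrepeated abnormality and no recorded adverse event, or to the laboratory comparison taken alone. Outcomes {12} also reports new or worsening laboratory values within groups at each visit without mentioning confirmation, and its named primary laboratory endpoint is the average change at week 8.

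Three stronger readings are tempting, and the article does not support them.

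- A reader might infer that every unrepeated abnormality is scored as no event. That is literal only for anemia. For the other tests it is an inference, and under the per-protocol rule the person may simply be excluded. The event is lost either way, but by a different route.
- A reader might infer that no repeat is planned after early departure. The visit table and flow figure are not shown, and closeout might be meant to include an early exit. The article does not say so, and uses the term for the end of follow-up.
- A reader might take the 25% attrition allowance as the share of events lost. It covers all causes of attrition, so the 25% rows are upper-end scenarios. Applying such a loss to 12 per arm while keeping all 12 would count attrition twice.

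Nor can the gap be left wholly to a statistical analysis plan: the article itself fixes the event definition, down to percentages and retest windows, and that definition does not work for a group the plan expects.

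**Conclusion.** The concern holds as a gap in the event definition. An abnormality at the last visit before an early departure cannot qualify as written (literally for anemia, through the parenthesis for the other tests) or is lost through per-protocol exclusion. The routes are departure by choice, for an adverse event, or for a dosing deviation.

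The bias is towards safety only if people who are unwell on XN leave more often, which is plausible but not shown. Its size cannot be fixed from the article. Under the assumed 55% against 5% at 16 per arm, power of 86% becomes 77% with a tenth of XN events lost and 60% with a quarter lost. These figures depend on the assumed base rate and on the share of abnormalities that go unrepeated; neither is given. The correction is worth making because it is cheap and the trial is small enough for one event to matter.

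**What to change.** Add to Outcomes {12}: an abnormality that meets the numeric criterion but has no repeat because the participant left early counts as an event in the between-group frequency comparison; such participants stay in that comparison despite the per-protocol rule in {20c}; and the confirmed-only count is reported as a sensitivity analysis.

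The second clause is needed, because counting the event achieves nothing if the person is then excluded. Leave the rule for completers, whose repeat falls after closeout, unchanged. A broader wording that accepted only repeats taken on study product would also count completers' week-8 abnormalities when the later repeat is normal, which goes beyond this problem.

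Cost: a short addition to the endpoint definition and one extra table. A few transient abnormalities in people who left will be counted, in both arms; the sensitivity analysis shows how much that matters.
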